**Trial protocol**

**Project summary**

**Objectives:** To form a unique body weight support-Tai Chi Yunshou (BWS-TCY) training method, apply it to the treatment of upper limb dysfunction after stroke, and provide a new safe and effective treatment method for the clinic.

**Methods and analysis:** A single-blinded randomized controlled trial will be conducted on 93 stroke patients. The patients will be randomly allocated into three groups: 1) conventional rehabilitation therapy (CRT) group; 2) CRT+BWS-TCY group; 3) CRT+ traditional RAT group. For the CRT group, participants will receive CRT treatments for 1 hour per day. For the CRT+BWSTY group, participants will receive 30-mins CRT treatments and 30-mins BWSTY training. For the CRT+RAT group, patients will receive 30-mins CRT treatments and 30-mins RAT training. All the interventions will be performed 5 days per week for a total of 12 weeks. The upper-limb functions will be assessed before and after the interventions using a series of rating scales and objective indicators.

**Expected results:** The 12-week BWS-TCY intervention may be effective in improving upper limb motor function.

**Background**

Stroke is an acute cerebrovascular disease caused by the sudden rupture or occlusion of blood vessels. It is divided into two main types: ischemic stroke, which accounts for 87% of cases, and hemorrhagic stroke, which accounts for 13%^[1]^. Ischemic stroke occurs when there is ischemia and hypoxia in the brain tissue around the blood vessel supply area, leading to a disruption of local blood supply and resulting in neurological deficits^[2]^. Hemorrhagic stroke is characterized by spontaneous intracranial hemorrhage, including cerebral hemorrhage and subarachnoid hemorrhage. It is typically caused by arterial rupture due to non-traumatic factors^[3, 4]^. Stroke is the second most common cause of death and the leading cause of disability worldwide^[5, 6]^. According to statistics from the World Health Organization, approximately 15 million people worldwide suffer from stroke every year. Out of these, more than 5 million people die from stroke and another 5 million people experience permanent severe disabilities^[7]^. Moreover, stroke often leads to severe complications in patients, including neuropsychiatric disorders and impairment of motor, sensory, and cognitive abilities^[8, 9]^. Among long-term stroke survivors, 70%-80% of patients will have various types of functional impairments^[10]^. This includes 48% with hemiplegia^[11]^, 22% who are unable to walk, and 24%-53% who are partially or completely dependent on daily life activities^[12]^. Additionally, 55-75% of them still experience upper limb dysfunction 3-6 months after the stroke onset^[13]^. This dysfunction is characterized by abnormal postures such as scapula withdrawal and sinking, shoulder joint flexion, adduction, internal rotation, elbow joint flexion, forearm supination, finger flexion, etc. Furthermore, 37% of patients have varying degrees of upper limb fine motor impairment^[14]^. Unilateral upper limb dyskinesia is a frequently observed complication^[15, 16]^. Individuals experiencing upper limb dysfunction often exhibit restricted joint movement, muscle contraction difficulties, and coordination disorders^[17]^. Following a stroke, upper limb dysfunction can greatly impede daily activities like eating, dressing, and washing^[18, 19]^. This limitation increases patients' reliance on others and negatively impacts their long-term quality of life^[20]^. Consequently, rehabilitating upper limb dysfunction becomes imperative in enhancing their functional capabilities.

Different rehabilitation techniques and various therapies can be used to restore upper limb function. One such technique is repetitive transcranial magnetic stimulation, a non-invasive brain nerve modulation technology that regulates the cortical excitability of cranial nerves to promote the recovery of upper limb motor function^[21, 22]^. Another technique, task-oriented bilateral training, focuses on training both the healthy and affected sides together^[23, 24]^. This helps the affected side imitate the movement pattern of the healthy side, stimulating the memory of corresponding muscles on the affected side and promoting the recovery of motor functions. Virtual reality technology creates a simulation environment that enables virtual interaction in sight, hearing, touch^[25]^. This technology fully engages patients in training and induces neuroplasticity through repetitive training, enhancing brain movement feedback. Mirror therapy uses visual feedback to compensate for reduced or missing sensory input in the affected upper limb and establish connections between limbs^[26, 27]^. By converting visual information into active behavior, the mirror neuron system is activated, promoting movement. Robot Assistant Training (RAT) integrates multiple disciplines such as rehabilitation medicine, robotics, situational interaction technology, and control engineering. It is based on the principles of neuroplasticity and motor relearning technology, and offers the advantages of quantification, individualization, and repeatability^[28, 29]^. Therapies that involve high-intensity repetitive tasks, like RAT, have been found to be highly effective in restoring upper limb function^[30]^. These therapies offer benefits such as high-intensity repetitive training, good visual feedback, and gravitational support^[31]^. However, it is important to note that RAT compensates for the affected upper limb through gravity, which can pose challenges to the patient's compliance during the exercise and consequently impact the treatment results^[32]^. Therefore, body weight support (BWS) may not be the most suitable option for long-term rehabilitation of upper limb dysfunction after a stroke and for improving the mental health of patients. Tai Chi is a traditional Chinese aerobic exercise that involves whole-body movements, including limb wrapping, to help patients regain lost neuromuscular functions^[33]^. Specifically, Tai Chi Yunshou (TCY) is a low-impact, moderate-intensity exercise that focuses on upper limb movement training. Studies have shown that TCY is effective in improving stroke stability, endurance, coordination, and motor function^[34-36]^. What sets TCY apart from other exercise interventions is its emphasis on high coordination of the upper limbs, complex motor control, and hand-eye coordination. This type of exercise activates the cerebral cortex and brain regions to a greater extent, leading to long-term enhancement or remodeling of functional connections in the brain^[36]^. However, completing TCY exercises requires better motor functions, such as muscle strength (Lovett >2) and joint range of motion^[37]^. Additionally, TCY exercise is generally suitable for patients in the late stage of stroke (Brunnstrom stage >3)^[35]^. Unfortunately, these abilities are nearly impossible for most early-stage stroke patients. Therefore, it is crucial to develop interventions that are simple and not limited by functional impairment. These interventions should be included in current stroke rehabilitation programs to enable patients to persist in training and obtain sustained benefits from treatment.

Previous studies have demonstrated that body weight supported Tai Chi gait training, using a suspension device within a balance bar, can enhance lower limb motor function and balance in early-stage stroke patients^[38, 39]^. However, this type of training typically requires the assistance of two therapists simultaneously, which can be time-consuming and labor-intensive. Rehabilitation robots, equipped with exoskeletons and robotic arms, have the capability to provide auxiliary, resistance, and passive training. These robots can also offer gravity compensation and have been shown to offer maximum flexibility in weight support and control strategies^[40]^.

The effectiveness of TCY in the late stage of stroke for upper limb rehabilitation has been confirmed by previous studies^[35, 41]^. However, according to the guidelines of the American Stroke Association, early rehabilitation intervention leads to better outcomes^[42]^. Therefore, our research focuses on exploring the use of TCY in the early stage of stroke. Previous studies have demonstrated that weight-reduced Tai Chi footwork training, utilizing a suspension device within a balance bar, improves lower limb motor function and balance in patients with early-stage stroke^[38, 39]^. By incorporating Tai Chi with suspension devices, patients who are unable to fully bear weight can initiate training promptly. However, this training method requires the presence of at least two therapists simultaneously, resulting in time and labor consumption. Rehabilitation robots, on the other hand, offer gravity compensation and are user-friendly^[40]^. Rehabilitation robotic exoskeletons and joysticks not only provide gravity compensation but also offer power-assisted training, resistance training, and passive training. The exoskeleton provides maximum flexibility in terms of weight support and control strategies, making it easily adaptable and usable in clinical settings.

Based on the aforementioned benefits, we have developed a program utilizing a rehabilitation robot to facilitate the completion of TCY movements by driving the affected upper limb with the robot's mechanical arm. Therefore, BWS-TCY may be a suitable exercise for enhancing upper limb function in stroke patients due to its unique exercise method. Firstly, participants are required to maintain stability in their upper limbs during TCY in order to ensure smooth movements, making TCY an effective way to stimulate muscle contraction in the upper limb. Secondly, patients face challenges in controlling their speed and frequently adjusting incline angles during training. By performing TCY, coordinated movements can be trained and the flexibility of upper limb joints can be improved. Moreover, patients are required to recall and reproduce these movements during training, which can enhance their cognitive abilities, hand-eye coordination, and sense of realism. Lastly, the robot system provides vivid and engaging animations as visual feedback to enhance patient motivation during training. Therefore, TCY holds great potential in promoting the recovery of upper limb function and improving the mental well-being of stroke patients. The use of BWS-TCY can facilitate better and faster learning of TCY movements, enabling stroke survivors to independently practice at home after discharge without the need for professional guidance or supervision. Enhancing the ability of stroke survivors to carry out their own rehabilitation plans anytime and anywhere should also be considered an important rehabilitation goal.

We will propose a novel intervention using BWS-TCY to test whether it has a better rehabilitation effect than RAT in stroke patients. This study will include three groups: conventional rehabilitation treatment (CRT) group, CRT+BWS-TCY group, and CRT+ RAT group. We will hypothesize that the three groups would show differential improvements in upper limb motor function, motor control, and joint range of motion. The findings of this study will contribute to optimizing the existing rehabilitation treatment process by integrating rehabilitation intervention, aiming to intervene in rehabilitation treatment earlier and more effectively. Additionally, it will provide stroke patients with a reference for choosing rehabilitation training programs.

Study goals and objectives

**Study design**

This study will be a single-center, three-arm, parallel-group, assessors-blind randomized controlled trial. All the patients will be informed of the study content before the subject recruitment. The patients who meet the inclusion criteria and agree to participate in the study will sign the informed consent. As shown in the study flow chart (**Fig.1**), the patients will be randomly allocated into 3 groups with equal sample size: 1) CRT group; 2) CRT+RAT group; 3) CRT+ BWS-TCY group. The rehabilitation interventions will last 4 weeks. Patients’ upper-limb functions will be assessed using rating scales before and after the interventions.

[figure not shown]

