**3 Sample size**

We utilized G*Power software (v3.1.9.2, University Dusseldorf, Germany; available for download from http://www.psychologie.hhu.de) to determine the sample size for our study. The primary outcome evaluation index considered in this study was FMA-UE. Prior to commencing the formal experiment, 15 patients who met the inclusion criteria were divided into groups in a 1:1:1 ratio. Sample size calculation was conducted for the main objective, which focused on the treatment effect 4 weeks after surgery. The results of the preliminary experiment revealed the following mean ± standard deviation values after 4 weeks of intervention: TCY+CRT treatment (35.5±9.5), RAT+CRT treatment (34.28±9.58), and CRT alone (29.00±10.2). Based on the G*power two-factor repeated measures analysis of variance (ANOVA) F test, a total sample size of 84 cases was determined for a two-tailed test with a power of 80% and a significance level of 5% (alpha error). Considering a 1:1:1 allocation ratio and accounting for a 10% dropout rate, we estimated that a final total of 93 patients (31 in each group) would be required.

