**6 Interventions**

All patients will receive rehabilitation intervention in addition to routine medical treatment and daily care in the hospital. The patient's safety status will be continuously recorded throughout the intervention. The rehabilitation intervention will last for 12 weeks, with sessions of 60 minutes per day, 5 days per week.

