**6.3 Intervention plan for BWS-TCY+CRT group**

In the CRT+BWS-TCY group, patients undergo 30 minutes of CRT treatment and 30 minutes of BWS-TCY training daily. During BWS-TCY training, patients will watch videos and learned TCY movements with the assistance of professionally trained therapists. They will be required to skillfully apply these movements. The exoskeleton rocker of the rehabilitation robot, which can customize the TCY movement trajectory, helped the patients with restricted limbs to complete TCY movements. The training process will involve the following steps: 1) Sitting upright, relaxing the body naturally, keeping the head upright, and maintaining direct eye contact with the person on the screen in front. This top-down conscious guidance facilitated overall body relaxation. 2) The affected forearm will be fixed on the handle, with the hand in an extended position. 3)The patient will follow the pre-saved TCY motion trajectory, allowing the robot's mechanical arm to assist in carrying out the TCY action. This will involve moving the shoulders, elbows, and wrists together to draw a circle clockwise from top to bottom and from inside to outside. Studies have demonstrated that as the weight support ratio increases, the degree of muscle activation gradually decreases^[38]^. Therefore, the weight support ratio was set at 40% at the beginning of the 12-week intervention program. The program followed the principle of starting from easy to difficult and repeating intensively. It was divided into 5 different weight support stages: Weeks 1-3: 40%; Weeks 4-7: 30%; Weeks 8-10: 20%; Weeks 11-12: 0%.

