**8 Statistical method**

The clinical data will follow the per-protocol (PP) analysis and intention-to-treat (ITT) analysis. PP analysis was applied to all the randomized participants who will not stop treatment prematurely, and complete 4 weeks of treatment. ITT analysis is applied for participants who have dropped out of the trial, according to the rule of last-observation-carried-forward. The normality test of the measurement data is performed using the Shapiro-Wilk method, and the conformity distribution is expressed as the mean ± standard deviation. P<0.05 is significant for the difference. Categorical data, such as gender or those expressed as frequencies (%) will be analyzed using the chi-square test or Fisher’s exact test. Perform nonparametric statistical tests on data that do not conform to the normal distribution. In addition, statistically significant differences in intra-group and inter-group data will be analyzed by repeated measurements of ANOVA. All statistical analysis will be performed using IBM SPSS version 25.0 (SPSS Inc., Chicago, IL, USA). Missing data patterns will be analyzed by missing value analysis.

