**Follow-up**

All participants will be followed up for 12 weeks after the intervention.

Data management and statistical analysis

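### The intervention is 4 weeks long in the Study design but 12 weeks elsewhere, so the primary FMA-UE time point, the sample-size basis and the per-protocol threshold do not line up

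*Protocol*

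**What the plan says.** Two intervention lengths stand in the current protocol text.

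**Four weeks**
- Study design: "The rehabilitation interventions will last 4 weeks".
- Section 3, Sample size: "Sample size calculation was conducted for the main objective, which focused on the treatment effect 4 weeks after surgery". The pilot figures given there are mean and "standard deviation values after 4 weeks of intervention".
- Section 8, Statistical method: "PP analysis was applied to all the randomized participants who will not stop treatment prematurely, and complete 4 weeks of treatment".

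**Twelve weeks**
- Project summary: "All the interventions will be performed 5 days per week for a total of 12 weeks".
- Section 6, Interventions: "The rehabilitation intervention will last for 12 weeks, with sessions of 60 minutes per day, 5 days per week".
- Section 6.3, which gives the BWS-TCY weight-support ratios as "Weeks 1-3: 40%; Weeks 4-7: 30%; Weeks 8-10: 20%; Weeks 11-12: 0" per cent.
- The sections on expected outcomes and on duration of the project, both of which describe a 12-week intervention.

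FMA-UE is the primary outcome (sections 3 and 7.1). The Project summary and Study design place the outcome assessments before and after the interventions and give no week number. The Follow-up section adds: "All participants will be followed up for 12 weeks after the intervention".

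**The concern.** The two lengths cannot both hold, and no text presents week 4 as an interim or primary visit within a 12-week course. The 4-week figure also sits in the places that fix the statistics: the main objective behind the sample size and the definition of an analysis set. Correcting the one sentence in Study design would leave those two untouched.

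What is at stake is the time point of the primary comparison. If it is week 12, the trial tests the whole programme but is powered on a 4-week effect. If it is week 4, the power basis fits, but the result covers only the first third of the programme, while the expected conclusion concerns all 12 weeks. With both figures in the protocol, the choice could be made after the data are seen. The per-protocol set is exposed in the same way, since it can be built by two different rules.

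**Working it through.** **1. Treatment dose.** Inputs: 5 days per week and 60 minutes per day (section 6).
- 4 weeks: 4 × 5 = 20 days, or 20 hours.
- 12 weeks: 12 × 5 = 60 days, or 60 hours.
- Ratio: 20/60 = 33%.

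**2. Which treatment has been given by week 4.** Input: the schedule in section 6.3.

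| Support | Weeks | Number of weeks | Given by week 4 | Still to come |
|---|---|---|---|---|
| 40% | 1–3 | 3 | 3 | 0 |
| 30% | 4–7 | 4 | 1 | 3 |
| 20% | 8–10 | 3 | 0 | 3 |
| 0% | 11–12 | 2 | 0 | 2 |
| Total | | 12 | 4 | 8 |

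At week 4, 8 of the 12 programme weeks are outstanding, including all 3 + 2 = 5 weeks at 20% or 0% support.

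**3. The plan's own sample size.** Inputs from section 3: 4-week FMA-UE of 35.5 ± 9.5, 34.28 ± 9.58 and 29.00 ± 10.2; alpha 5%; power 80%; total N = 84; dropout 10%; final N = 93.
- SD of the three means (divisor 3) = 2.82. Pooled SD = √[(9.5² + 9.58² + 10.2²)/3] = 9.77. Cohen's f = 2.82/9.77 = 0.289.
- Repeated-measures ANOVA, between-groups test: noncentrality λ = f²·N·m/[1 + (m − 1)ρ], with 2 and N − 3 degrees of freedom, m measurements and correlation ρ. The protocol gives neither m nor ρ, so these are assumed: m = 2 needs N = 79 (ρ = 0.3) or 90 (ρ = 0.5); m = 3 needs 81 (ρ = 0.5) or 96 (ρ = 0.7).
- Group-by-time interaction: λ = f²·N·m/(1 − ρ). With m = 2, N runs from 61 (ρ = 0) down to 15 (ρ = 0.8).
- One-way ANOVA at a single time point: N = 119.
- Dropout: 84 × 1.1 = 92.4, rounded up to 93. The alternative 84/0.9 = 93.3 would give 94.

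The stated 84 lies within the between-groups range but can be neither confirmed nor refuted without m and ρ. For the present point, what matters is that every outcome value entering the calculation is a 4-week value. The protocol gives no 12-week mean or SD, so no N or power for a week-12 comparison can be computed from it.

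**4. Per-protocol rule.** Section 8 joins two conditions: no premature stop, and 4 weeks completed. In a 12-week course, take a patient who stops after week 6, that is, after 6 × 5 = 30 of 60 days. This patient satisfies the second condition. Read literally, the first excludes the patient, which leaves the 4-week condition with no work to do. If 4 weeks is instead meant as the definition of adequate completion, the patient stays in, and the threshold is 33% of the planned days.

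**5. End of follow-up.** With 12 weeks of follow-up after treatment, the last contact is at 4 + 12 = 16 weeks under Study design, or 12 + 12 = 24 weeks under the other sections.

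**The case against.** The strongest reply is that delivery is not really in doubt. The operative Interventions section, the week-by-week schedule and the stated project duration all say 12 weeks, and only one overview sentence gives 4 weeks as the intervention length. On that view the 20-against-60-day contrast describes a course nobody will give, and week 16 as the end of follow-up arises only if the project-duration section is set aside. This largely stands: 12 weeks is the likelier intention, and the follow-up discrepancy is minor.

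It can also be argued that section 3 does name a time point, 4 weeks, and that a 4-week primary analysis inside a longer programme is a legitimate design compatible with repeated-measures ANOVA. The study flow chart is not available here and may list visits. That is possible, but no available text schedules a week-4 assessment or calls it primary. A visit chart could clarify the assessments but could not reconcile the written durations.

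On the per-protocol rule, two conditions joined by "and" are better read as redundant than as contradictory. That is fair, but a redundant 4-week threshold in a 12-week course still invites the looser reading.

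Finally, sizing a longer trial on short-term pilot data is an assumption rather than an error in itself, and no loss of power has been shown. That is also right; the criticism is that the protocol does not present it as an assumption. The reference to surgery, in a trial without any, is a separate drafting slip.

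**Conclusion.** The concern holds and needs correcting. The protocol gives two intervention lengths, 4 and 12 weeks. The 4-week figure governs the sample-size objective and the per-protocol set, while the 12-week figure governs treatment delivery and the expected conclusion.

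If 12 weeks is correct, the likelier reading, the error lies in Study design, and sections 3 and 8 are misaligned with the trial as run. The 80% power then applies to a point when 20 of 60 treatment days have been given, and its value at week 12 is unknown. If 4 weeks is correct, the support schedule, the expected outcomes and the project duration are wrong.

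This rests on the written text alone; the flow chart could not be seen. It does not claim that 84 or 93 is too small, and no replacement N is proposed.

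**What to change.** - State one intervention length throughout. Twelve weeks appears intended; the sponsor should confirm it and correct Study design.
- Name FMA-UE at one specified week as the primary comparison and make the other visits secondary.
- In section 8, set the per-protocol threshold to match that length: either full completion or a stated share of the planned treatment days (of 60, if 12 weeks is confirmed).
- In section 3, remove the reference to surgery and state that the calculation uses 4-week pilot data, so that the 80% power is for a 4-week effect and is an assumption if week 12 is primary.
- If week 4 is deliberately primary within a 12-week course, say so, schedule that FMA-UE assessment in the text and limit the primary conclusion to week 4.

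The cost is mainly amendment wording. Choosing week 12 makes the power statement less firm, and the sponsor may need to review N. Choosing week 4 requires a stated assessment at that week and confines the primary conclusion to the first third of the programme.
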